## Abstract

**Background:**

Lynch syndrome (LS) is an inherited, cancer predisposition syndrome associated with an increased risk of colorectal, endometrial and other cancer types. Identifying individuals with LS allows access to cancer risk management strategies proven to reduce cancer incidence and improve survival. However, LS is underdiagnosed and genetic referral rates are poor. Improving LS referral is complex, and requires multisystem behaviour change. Although barriers have been identified, evidence-based strategies to facilitate behaviour change are lacking. The aim of this study is to compare the effectiveness of a theory-based implementation approach against a non-theory based approach for improving detection of LS amongst Australian patients with colorectal cancer (CRC).

**Methods:**

A two-arm parallel cluster randomised trial design will be used to compare two identical, structured implementation approaches, distinguished only by the use of theory to identify barriers and design targeted intervention strategies, to improve LS referral practices in eight large Australian hospital networks. Each hospital network will be randomly allocated to a trial arm, with stratification by state. A trained healthcare professional will lead the following phases at each site: (1) undertake baseline clinical practice audits, (2) form multidisciplinary Implementation Teams, (3) identify target behaviours for practice change, (4) identify barriers to change, (5) generate intervention strategies, (6) support staff to implement interventions and (7) evaluate the effectiveness of the intervention using post-implementation clinical data. The theoretical and non-theoretical components of each trial arm will be distinguished in phases 4–5. Study outcomes include a LS referral process map for each hospital network, with evaluation of the proportion of patients with risk-appropriate completion of the LS referral pathway within 2 months of CRC resection pre and post implementation.

**Discussion:**

This trial will determine the more effective approach for improving the detection of LS amongst patients with CRC, whilst also advancing understanding of the impact of theory-based implementation approaches in complex health systems and the feasibility of training healthcare professionals to use them. Insights gained will guide the development of future interventions to improve LS identification on a larger scale and across different contexts, as well as efforts to address the gap between evidence and practice in the rapidly evolving field of genomic research.

**Trial registration:**

ANZCTR, ACTRN12618001072202. Registered on 27 June 2018.

**Electronic supplementary material:**

The online version of this article (10.1186/s13063-019-3457-6) contains supplementary material, which is available to authorized users.

## Background

### Evidence translation for genetics and genomics

Advances in genetic and genomic research have promised to transform future approaches to disease prevention, detection and treatment [1, 2]. In the clinical setting, the development of high-throughput technologies for genetic sequencing and analysis has generated new opportunities for improved diagnosis of genetic disorders, personalised targeted treatments (particularly for cancer patients), prenatal screening and diagnosis, pharmacogenomics and population-based assessment of disease risk [3, 4]. However, the process of integrating these changes into existing healthcare systems has been slow and challenging, with health systems struggling to keep up with the exponential speed at which the genomics evidence-base is evolving [4–6].

Next-generation sequencing platforms have improved the affordability and feasibility of detecting rare, but highly penetrant mutations in cancer predisposition genes, such as *TP53*, *BRCA1, BRCA2, APC* and the mismatch repair genes - *MLH1, MSH2, MSH6* and *PMS2* [2]. With increasing recognition of the clinical utility of genetic information, the number of patients being offered genetic testing is increasing, putting pressure on specialist genetics services that have limited capacity to cope with the increased demand [1, 6]. Some genetics-related tasks have already been deployed to clinicians (sometimes termed “mainstreaming”), for example with surgeons or oncologists now ordering genetic tests and interpreting pathology reports to determine risk and whether to refer to genetics [6–10]. This requires incorporating new practices and behaviours; however, the success of these has been mixed (e.g. with suboptimal referral rates identified) [7, 11]. With more mainstreaming of genomics into health systems on the horizon, there is a need to understand how best to incorporate genetic responsibilities into clinical practice.

### Frameworks and theory to support implementation

Implementation science uses evidence-based strategies (e.g. system change interventions, quality monitoring tools) to promote the behavioural change necessary for effective implementation, and can be applied to all translational phases of the genomic research continuum to promote uptake in the clinical setting [5, 12]. Implementation science frameworks (e.g. the consolidated framework for implementation research (CFIR) [13]; reach, effectiveness, adoption, implementation and maintenance (RE-AIM) [14]; promoting action on research implementation in health services framework (PAHRIS) [15]) consolidate these strategies to provide guided, systematic approaches that can be used by researchers and/or clinicians to enhance implementation. However, a recent literature review demonstrated that less than 2% of studies aimed at translating genetics and genomics research into clinical practice explicitly made use of these implementation science frameworks [5]. Given the pace at which genomic research is expanding, failure to utilise evidence-based implementation frameworks is likely to widen the gap between evidence and practice [5].

Implementation frameworks with a theoretical basis can enhance understanding of the factors influencing implementation success or failure and have been proven effective in producing health system behaviour change across a number of settings [16–18]. One example is the theoretical domains framework (TDF), which synthesises a range of behaviour change theories to aid the identification of behaviour change barriers, which can then be specifically targeted by evidence-based interventions [19]. The TDF has been used extensively in clinical practice to promote healthcare professional behaviour change, but with variable success [16, 20–22]. Understanding factors that mediate intervention success across complex and unpredictable health systems remains a challenge [23, 24]. The success or failure of an intervention is likely to result from a complex interplay between a number of factors, including the nature of the clinical problem; novelty of proposed changes; appropriateness of the chosen implementation framework; attributes of the individual(s) driving the change (e.g. level of experience, psychosocial determinants) and contextual influences at local, organisational and system levels [25]. In such settings, rigorous trials of different implementation approaches may help to begin unravelling these complexities.

### Implementing Lynch syndrome evidence into practice

Lynch syndrome (LS) is one of the genetic syndromes that has been impacted by these implementation challenges. LS is an autosomal dominant cancer predisposition syndrome conferring an increased risk of colorectal, endometrial and other cancer types [26]. Identifying individuals affected by LS allows access to cancer risk management strategies (e.g. colonoscopic surveillance, risk-reducing hysterectomy) proven to reduce cancer incidence and improve survival [27, 28]. Despite guidelines recommending universal LS screening strategies for patients with LS-associated cancers, the condition remains largely underdiagnosed and current genetic referral rates are suboptimal [11]. In Australia, little is known about LS diagnostic pathways or the practices hindering rates of referral - partially owing to the challenges of linking data between hospitals, pathology providers and familial cancer clinics [29], as well as a lack of standardised referral pathways upon which these data can be mapped to identify system failures. Whilst Brennan and colleagues identified various stages at which cases of colorectal cancer (CRC) slipped through the LS referral cracks in hospitals in the Australian Capital Territory [11], further work is needed to establish practices at a national level.

Recently, a pilot study [30] was conducted at two large Australian hospitals to improve the identification of LS amongst patients with CRC using the theoretical domains framework implementation (TDFI) approach: a theory-grounded, 6-step approach that combines the TDF with implementation science principles to systematically promote behaviour change in accordance with clinical guidelines [16]. The following TDFI steps were carried out at each site: (1) local multidisciplinary teams formed to map current LS referral processes; (2) target behaviours were identified using discussion supported by a retrospective audit; (3) barriers to those behaviours were identified using the validated Influences on Patient Safety Behaviours Questionnaire (IPSBQ) and TDFI-guided focus groups; (4) interventions were co-designed to address barriers using focus groups; (5) interventions were co-implemented and (6) impact of the intervention was evaluated [30]. The rationale for this approach was to actively involve healthcare professionals throughout the implementation process, particularly by using their tacit knowledge to contextualise problems and co-design pragmatic interventions [31] alongside input from implementation experts with theoretical expertise in behaviour change [32].

The pilot study yielded mixed results, with changes in some behaviours (e.g. improved ordering of supplementary pathology tests, standardised wording of pathology reports) but no overall improvement in the primary study outcome (number of LS referrals) [30]. Post-implementation interviews were conducted with healthcare professionals involved in the LS implementation pilot study, with thematic analysis highlighting key implementation challenges across both theoretical and practical boundaries. These included (1) the accessibility of theory to healthcare professionals (e.g. lack of understanding and/or perceived necessity of behaviour change theory), (2) compliance with theory by healthcare professionals (e.g. a tendency to jump straight into solution generation rather than following TDFI steps), (3) navigating the system (e.g. lengthy governance processes, lack of external researcher knowledge about internal stakeholder networks and contacts) and (4) stakeholder management (e.g. lack of researcher awareness about existing internal politics and hierarchies).

### Refining implementation approaches and testing the impact of theory

One approach to solving both the theory-related and practical problems presented is to train healthcare professionals from within the system to use an implementation science framework as part of a research study, specifically the TDFI approach in this instance. Training healthcare professionals from within the system is likely to alleviate (1) theoretical barriers (accessibility and compliance) via education about the rationale and demonstrated benefits of a theory-based approach, and upskilling to ensure the approach is applied accurately and (2) practical barriers (navigating the system and stakeholder management) by drawing on knowledge from within the system about existing processes, bureaucracy and internal stakeholder networks and politics. Not only is this likely to enhance the feasibility of the TDFI approach for improving clinical practice in genomics, it is also likely to improve the fidelity of delivery of the approach, and the rigour under which it is tested - crucial challenges that need to be addressed to advance the field of implementation science [32].

Theoretically underpinned implementation frameworks can optimise and contextualise the design of behaviour change interventions, whilst increasing opportunities to understand generalizability to other settings [33]. However, to understand the impact of the use of theory in an implementation approach, and to advance the science of behaviour change in healthcare, it is important to distinguish the theoretical components (e.g. use of the TDF to identify barriers and generate targeted intervention strategies), holding as many of the other aspects of the implementation approach constant. Therefore, this study will compare the effectiveness of two identical, structured implementation approaches delivered by trained healthcare professionals, distinguished only by the use of theory to identify barriers and to design targeted interventions, in improving clinical practice for identifying patients with LS.

## Methods

### Design

This protocol is reported in line with the Standard Protocol Items: Recommendations for Interventional Trials (SPIRIT) checklist (Additional file 1) [34]. The results will be reported in line with the Consolidated Standards of Reporting Trials statement extension for social and psychological interventions (CONSORT-SPI 2018 extension) [35]. Consequently, the CONSORT-SPI flow diagram is reported in this protocol (see Fig. 1).

**Fig. 1 Fig1:**
[figure not shown]
Consolidated Standards of Reporting Trials statement extension for social and psychological interventions (CONSORT-SPI) flow diagram. Diagram of participant (hospital networks) recruitment. *Numbers to be incorporated as trial progresses

A parallel, cluster randomised trial will be used to test for differences between a theory-based implementation approach (TDFI) and a non-theory based implementation approach to improving LS referral practices in eight large Australian hospital networks across three states [New South Wales (n=4), Victoria (n=2), and Western Australia (n=2)]. As sharing of staff and resources in networked hospitals is likely to lead to correlations between outcomes, each hospital network will comprise a separate cluster in this trial (i.e. eight clusters in total). Hospital networks will be randomly allocated to the theory arm or non-theory arm using a computer-generated random sequence. To account for differences in region-specific LS detection pathways, the randomisation will be stratified by participating states, with the same number of networks from each state allocated to theory and non-theory arms (a 1:1 allocation ratio). A theory-based, mixed methods process evaluation will be conducted alongside the trial to investigate intervention fidelity, potential mechanisms of impact, mediators and contextual moderators, for both approaches [24, 36].

### Overview of implementation intervention

At each hospital network, a locally employed healthcare professional (see “Implementation Lead recruitment”) from within the system will be trained to lead a 7-phase implementation intervention approach (see “Procedure”).

### Outcomes

#### Pre-implementation outcomes

CRC surgery, pathology, and familial cancer clinic (FCC) clinical data will be retrospectively collected across all hospital networks for patients admitted during a 24-month period prior to study commencement, to demonstrate LS referral pathway clinical practice. The data will be cross-referenced with LS referral maps to be constructed for each hospital network. The proportion of patients who transition to each step, in adherence to the pathway map will be calculated, leading to the identification of bottlenecks. The referral maps and bottlenecks will be compared across hospital networks, with particular attention to potential differences in processes between geographical regions. A validated TDF-based questionnaire (Influences on Patient Safety Behaviours Questionnaire) [37] will be used to quantitatively evaluate psychosocial barriers to risk-appropriate completion of the LS referral pathway. Qualitative focus group data will be used to understand key barriers in context.

#### Post-implementation outcomes

The primary post-implementation quantitative outcome will be the change in the proportion of patients with risk-appropriate completion of the site-specific LS tumour testing and referral pathway within 2 months of CRC resection. Secondary outcomes will be (1) proportion of high risk-patients who were referred to the FCCs (sensitivity of referral), (2) proportion of referred patients who attended FCC and (3) proportion of patients with missing testing and referral data.

### Recruitment

#### Study site recruitment

The research team approached ten Australian hospital networks to participate. Due to the difficulty of obtaining the number of CRC resections performed by hospital per year, the eligibility criteria used to identify networks was defined as “hospitals where CRC resections are routinely performed”. A hospital network may consist of a single hospital or several hospitals (including co-located or off-site pathology laboratories and FCCs) in which staff and resources are shared. In each cluster, at least one hospital of > 500 beds is included. The Chief Investigator steering committee (see Additional file 2 for study personnel roles and responsibilities) was consulted to identify hospitals to approach to participate. Of the ten hospital networks approached, two were excluded. Research governance applications for eight networks (each consisting of 1–3 individual hospital sites) are being prepared for or reviewed by hospital research governance offices, and formal enrolment will be concluded when research governance approval is granted for each hospital network. No exact numbers of patients with colorectal cancer who undergo resection were available for the individual hospitals; rough estimates are 100–250 per hospital network per annum.

#### Implementation Lead recruitment

At each hospital network, a locally employed healthcare professional will be appointed as a paid Implementation Lead for one day per week over a 24-month period to coordinate the implementation approach and to oversee data collection. They will have a professional understanding of the LS patient pathway, and the ability to motivate other LS stakeholders to engage with implementation processes. These criteria will be used to select the most appropriate candidate for the Implementation Lead role at each hospital network.

#### LS patient pathway stakeholder recruitment

Using snowball recruitment methods, stakeholders in the LS patient referral pathway (e.g. surgeons, pathologists, oncologists, registrars, genetic counsellors) will be invited by the Implementation Lead to participate in one or more study activities relevant to their role at timepoints throughout the implementation approach. These include process map meetings, questionnaires, focus groups and intervention implementation planning meetings.

### Allocation and concealment

Block randomisation for this study was carried out at the level of the hospital networks. Each hospital network (and associated pathology laboratory and FCC) was allocated to the theory arm or non-theory arm by a member of the research team not involved in recruitment of hospital networks, using a random computer-generated sequence, with stratification by state. The research team will be aware of the trial arm allocation to train the Implementation Leads; however, the allocation will be concealed from the Implementation Leads, and the individual participants they recruit [Implementation Team members (see Phase 2) and LS patient pathway stakeholders]. Following randomised allocation, Implementation Leads were trained in one of two structured implementation approaches: either a theory-based approach or a non-theory based approach. Allocation has been concealed from the Chief Investigators. To prevent selection bias, all hospital networks were recruited prior to randomisation, and all adult patients undergoing a CRC resection at each hospital network within the study timeframe will be included in the study. Currently, there are no anticipated circumstances when unblinding would be considered permissible. Given the inability to fully control interactions between individuals at different networks involved in the trial, we accept that masking of Implementation Leads and individual participants may be compromised. Plans to investigate the success of masking amongst Implementation Leads are being incorporated into the process evaluation.

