## Measures

### Clinical data collection

Patient-level clinical practice data relating to the CRC and LS referral pathway will be extracted from relevant surgical, pathology, and FCC databases by the Implementation Leads (see Additional file 2 for variables). Patient data will be collected throughout the implementation of the intervention, and outcome data will be collected for up to 9 months after the end of the intervention strategies. Patients will be eligible for inclusion if they undergo CRC resection at participating hospital networks within the time periods for data collection and are aged over 18 years at the time of resection. Given the short duration of the trial and minimal risk of harm, a formal data monitoring committee will not be required. An ethics-committee-approved data management plan has been presented to research governance officers and will be refined for each participating hospital network to ensure compliance with site-specific protocols.

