#### Phase 1 - undertake baseline audit

The Implementation Leads at each site will undertake data extraction using the clinical practice data extraction tool to establish baseline evidence on existing LS referral practices (see Additional file 2 for data variables). These data will be de-identified and securely transported to the research team. The research team will carry out data checks and undertake site specific analyses for the purpose of presenting local results back to each site.

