##### Theory-based implementation arm

Focus group participants will be made aware that the IPSBQ assesses barriers according to theoretical domains explicitly linked to the identification of behaviours. They will be presented with the IPSBQ results from their site, discuss barriers in the context of the TDF and come to a consensus about the top 3–4 barriers overall. The research team will undertake a theory-based analysis of the focus group data to generate an initial implementation package, based on identification of intervention strategies informed by behaviour change techniques (BCTs) matched to identified barriers. This package will be discussed and refined by the Implementation Lead and the research team.

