##### Theory-based implementation arm

Focus group participants will be presented with a table of barriers mapped to the TDF and solutions mapped to BCTs.

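### The claimed masking is not credible for the theory arm as described, and the article describes no masked person in extracting, checking or classifying the outcome

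*Protocol article*

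**What the plan says.** **Masking.** The protocol article (Allocation and concealment) states that "the allocation will be concealed from the Implementation Leads, and the individual participants they recruit". Of the others involved it says "The research team will be aware of the trial arm allocation to train the Implementation Leads" and "Allocation has been concealed from the Chief Investigators". It adds that "we accept that masking of Implementation Leads and individual participants may be compromised", because contact between people at different networks cannot be fully controlled, and it plans to examine masking among Leads in the process evaluation.

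**Arm content.** Training differs between arms by the added TDF material in the theory arm (Implementation Lead training and ongoing support). Leads run the focus groups in the format of their arm (Phase 4). In the theory arm, "Focus group participants will be made aware that the IPSBQ assesses barriers according to theoretical domains", and participants see their site's results. In Phase 5 they are "presented with a table of barriers mapped to the TDF and solutions mapped to BCTs". Non-theory participants fill in the same questionnaire (IPSBQ), do not see its results, and are given intuitively derived barriers and solutions.

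**Outcome data.** Patient-level data "will be extracted from relevant surgical, pathology, and FCC databases by the Implementation Leads" (Clinical data collection). At baseline, "The research team will carry out data checks and undertake site specific analyses" (Phase 1). The Lead drafts the site's pathway map and later refines it with the research team (Phase 3). The primary outcome is completion of that site-specific pathway within 2 months of resection (Post-implementation outcomes). Missing test or referral data are counted as not done (Assessing clinical practice change).

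**The concern.** The article makes a masking claim that its own procedures undercut, and it names a lesser route of failure while passing over the main one. This matters because the Leads, who run the change at their site, also collect the data by which the change is judged. They know whether a record falls before or after implementation, which is the exposure in the planned regression. The team that receives the data knows the arm.

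The outcome depends on finding evidence of tests and referrals in surgical, pathology and familial cancer clinic databases. Evidence that is not found scores as failure. A difference in search effort between periods would therefore appear as an effect of implementation. A difference between arms in that change would appear as an effect of theory, which is the question the trial is meant to answer.

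**Working it through.** The article states no figure on this point, so the check is mainly textual.

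**Step 1: each role, its stated masking, and its part in the outcome**

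| Role | Stated masking | What the role is told, shown or does | Part in the outcome |
|---|---|---|---|
| Lead, theory arm | Concealed | Trained with TDF content; runs TDF-based focus groups | Extracts patient data; drafts the map |
| Lead, non-theory arm | Concealed | Trained without TDF content; runs generic focus groups | Same |
| Participants, theory arm | Concealed | Told the questionnaire measures theoretical domains; see its results and a TDF and behaviour-change-technique table | None stated for extraction |
| Participants, non-theory arm | Concealed | Complete the questionnaire without feedback; see intuitive barriers and solutions | None stated for extraction |
| Research team | Aware | Trains and supports Leads | Checks and analyses baseline data; refines the maps |
| Chief Investigators | Concealed | Not described | None stated |

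Theory-arm Leads and participants therefore know that they are using a theory-based approach. The Background also says that training in this approach educates Leads about its rationale and demonstrated benefits. What they may not know is that another arm works without theory, or that this contrast is under test. Nothing shown to the non-theory arm states its allocation.

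**Step 2: the path of the outcome data.** Extraction is by Leads, checking (stated for baseline) by the aware team, and map definition by Lead and aware team together. Under Trial status, networks had been randomised while phases 1–7 and data collection had not begun. The maps are thus drawn after allocation. The only other group stated to be concealed, the Chief Investigators, has no described place in this path.

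**Step 3: how unequal capture enters the result.** Let *p* be the true completion proportion and *c* the chance that a truly completed pathway is fully found in the records. Assume that no incomplete pathway is recorded as complete. Under the missing-means-not-done rule:

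- observed proportion = *p* × *c*
- observed post/pre ratio = true ratio × (*c* post ÷ *c* pre)

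With no true change (true ratio 1), whatever the value of *p*:

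- capture 95% post, 90% pre: 0.95 ÷ 0.90 = 1.06
- capture 95% post, 85% pre: 0.95 ÷ 0.85 = 1.12

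For the contrast between arms, the distortion is the theory-arm capture ratio divided by the non-theory-arm capture ratio. If both arms move from 90% to 95%, it is 1.06 ÷ 1.06 = 1.00. If only one arm does, it is 1.06. All capture values are assumptions; the documents give none.

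Unequal capture needs no intent. Baseline data are collected retrospectively over 24 months, whereas later data are collected during and after implementation by a Lead already working on the pathway.

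**The case against.** **Knowing one's procedures is not knowing the arm.** A reader might infer that masking is impossible in both arms. The documents do not support that. Both arms get an introduction to implementation science and the same seven-phase structure, and withheld questionnaire results reveal nothing unless one knows that others see theirs. This stands, and limits the point to the theory arm.

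**The weakness is disclosed.** The article accepts that masking may be compromised and plans a check among Leads. This stands in part: the stated cause omits the intervention content, and no check among participants is mentioned.

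**Leads are not said to judge completion.** They extract listed variables from existing databases, at baseline with an extraction tool, and all adults undergoing resection are included. This stands. The discretion left to Leads lies in how thoroughly evidence is sought, not in who enters the denominator or, as far as the text shows, in the classification.

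**Absence of any masked step is inferred from silence.** A reader might conclude that the whole trial lacks masked assessment. The article does not say who derives the post-implementation outcome or fits the model, and the full protocol or analysis plan may provide for masking there. This stands; the point concerns only what is described.

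**Equal effort cancels.** Similar extraction in both arms leaves the ratio contrast largely unaffected, and the proportion with missing data is already a secondary outcome that could expose unequal capture. Both are fair, but the pre/post comparison within each arm would still be distorted.

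**Conclusion.** The point holds in limited form. The concealment statement is not credible for theory-arm Leads and participants, who can be masked at most to the comparator or hypothesis. Outcome extraction rests with Leads; baseline checks and refinement of the outcome-defining maps involve a team that knows the allocation; and no masked person is described at those steps.

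The text does not show that bias will occur, nor how large it would be. The ratios of 1.06 and 1.12 illustrate the mechanism under assumed capture rates and no false completions; they are not estimates. The change is worth making because it is cheap and, as the article stood, data collection had not started. It is not a ground for calling the design invalid.

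**What to change.** 1. Restate Allocation and concealment so that Leads and theory-arm participants are described as masked at most to the hypothesis, and name the intervention content as a route of unmasking alongside contact between networks.
2. Confirm that Leads export only raw dated events (resection, each test, referral, attendance), with the same extraction tool in both periods.
3. Lock each network's pathway map and the completion algorithm before post-implementation data are extracted.
4. Have completion derived by an existing team member with no part in training or support, on a file with arm and period removed and dates given as days since resection. Restore labels and calendar intervals once the outcome file is locked.
5. Report the missing-data secondary outcome by arm and period. Masked derivation cannot repair unequal capture at extraction, so this check is needed as well.

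The cost is a small delay, protocol wording, reassignment of one task, and relinking of dates for the 3-month covariates. Site feedback analyses must be kept apart from the trial outcome file. Masking will remain imperfect, because with eight networks a site-specific map may identify its network.
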